#### Recruitment not-in-care cohort

Not-in-care participants will be recruited at a variety of front-office, social support and primary care services. These include homeless shelter services (*n* = 3), financial and administrative support services (*n* = 1), social care services (*n* = 2), and integral community support teams (*n* = 7). Due to uncertainty about meeting the first three SMI criteria, professionals from these services will be asked to select participants from their caseload based on client histories and their professional assessment with regard to meeting specifically the last SMI criterion of the study (i.e. coordinated care from professional care providers, embedded in local health care networks, is indicated to perform and effectuate the treatment plan for the *assumed* psychiatric disorder). A definitive validation of meeting the inclusion criteria with respect to SMI will be made on the basis of their responses on a selection of items concerning psychiatric symptoms in the questionnaire, current levels of general functioning and mental health treatment history. As such, it is possible that people who participated in interview 1 may still be excluded from the final study sample (they will receive an incentive for their time and effort).

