**Methods:**

A cohort design will be used. A representative sample of community-dwelling adults with an SMI, including those in care (*n* = 650) and not in care (*n* = 150), will be followed over time. During a two-year time period, participants will be interviewed twice using a wide-ranging set of validated instruments. Interview data will be matched with administrative data about the care process, as retrieved from their patient files. Primary outcomes are changes over time in recovery, societal participation and quality of life, controlled for the occurrence of adverse life-events during follow-up. Additionally, prevalence estimates of and associations between social functioning, safety and discrimination, substance use and health indicators will be investigated.

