### Setting

The study is situated in Amsterdam, the Netherlands. Internationally, the prevalence of SMI in the general population is estimated to vary between 0.5–2.9% according to, amongst others, population density, age distribution, social economic indicators, the number of (ethnic) minorities and the level of social cohesion [34–38]. Concerning specifically Amsterdam, reliable figures about the number of inhabitants with an SMI are lacking. The most recent 12 month-prevalence estimates vary between 1.6% [31] and 2.0% [30, 39], equaling an SMI population of between 7923 and 9827 adults within the municipality, of whom approximately 90% are considered community-dwelling and 10% to reside in long-term clinical settings [40].

The city of Amsterdam is subdivided into 8 administrative districts of which 7 residential districts and 1 industrial/harbor district. Together, the residential districts consist of 476 distinct neighborhoods, conglomerated into 99 quarters (or combined neighborhoods). Participants will be sampled and recruited at the level of quarters. As such, the resulting sample is designed to be representative at the level of the city, the city-districts and the quarters. From each of the residential districts, the two largest quarters are selected (based on population size, ranging from 12,946 to 26,787 registered residents). Together, these 14 quarters comprise 104 neighborhoods, 4437 unique postal codes and 237,157 inhabitants [38]. Within these quarters, prevalence estimates of SMI range between .02 and 3.08% [36] and an average SMI prevalence of 1.6% of the adult population of these quarters is assumed.

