#### Exclusion criteria

The following exclusion criteria will be applied:people with an intellectual and/or physical disability who are not in need of mental health care for co-morbid psychiatric disorders;people who suffer from dementia and who are not in need of mental health care for co-morbid psychiatric disorders;people who meet all inclusion criteria but whose formal postal code of their home address matches those of long-term clinical locations of mental health care providers (i.e. not community-dwelling patients);people whose proficiency in either Dutch or English is insufficient to be interviewed, and people who cannot be approached due to other mental health or social problems.

Within the larger population of community-dwelling adults with an SMI, the study differentiates between three cohorts. First, the ‘in-care cohort’ consists of adults with an SMI who receive ambulatory mental health care. Second, the ‘not-in-care cohort’ is formed by adults with an SMI who do not receive specialized mental health care from a formal mental health care provider yet may receive social welfare/support. Third, the ‘LZA-cohort’ are participants of a former longitudinal cross-sectional study into long-term care-dependent psychiatric patients in Amsterdam, carried out in 2005 and 2012 by Amsterdam’s largest mental health care providers Arkin and GGZ inGeest (in Dutch: the Langdurige zorgafhankelijkenstudie or LZA-study). This study focused on the psychological and social functioning and quality of life of people with a chronic SMI [32, 45]. Participants of the LZA-study who provided written consent to be re-approached were eligible to participate in the current study. The reason to include this LZA-cohort is that the current study utilizes a similar set of instruments which enables a third measurement for the LZA-study, providing insight in long-term (2005–2020) developments of this subgroup within the population of people with SMI.

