With respect to the in-care and not-in-care cohorts, their relative proportions within the total SMI-population in Amsterdam are approximately 76 and 24%, respectively [30]. Furthermore, around 90% of both groups lives independently (i.e. community dwelling). In-care participants will be recruited at the two largest mental health care providers in Amsterdam, Arkin and GGZ inGeest. Together, these organizations are estimated to provide care/treatment to two thirds of the total in-care population of people with an SMI in Amsterdam [39]. The remaining 33% of the in-care SMI-population, those who receive mental health care from one of several other (small) providers, will not be included as we expect to obtain a representative sample of the in-care population from the selected service providers. Moreover, recruiting participants at numerous care providers would require a disproportional effort and is therefore considered unfeasible. The ‘not-in-care’ participants will be recruited at a variety of social welfare and social support organizations in Amsterdam, including organizations that target the homeless (e.g., HVO-Querido, Leger des Heils, Cordaan, Volksbond). In this group, the SMI-criteria will be assessed during the interview.

As such, on the basis of 1) the assumed average SMI prevalence of 1.6% among the adult population of the selected quarters (237,157 * 1,6% = 3795 people), and 2) the proportion of adults with an SMI who are registered as a mental health care patient (76%, *n* = 2884), and 3) of whom at one of the two main mental health care providers in the city (66%, *n* = 1903) and 4) the proportion within this group who live independently (i.e. community dwelling) (90%), the in-care cohort is estimated to consist of 1739 adults with an SMI. On the basis of the aforementioned proportions, the not-in-care cohort is estimated to consist of 820 people. The LZA-cohort potentially consists of 157 former LZA-participants who gave permission to be re-approached. Based on expected response rates of 33% in the in-care cohort, 20% in the not-in-care cohort and 50% in the LZA-cohort, the study sample will consist of approximately 800 participants. Figure 1 presents a flowchart depicting the composition of the study population.

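### The not-in-care cohort is defined and sized as all untreated community-dwelling adults with SMI, but every named recruitment route is a service caseload, so the claim to represent that group is not supported

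*Protocol article*

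**What the plan says.** **Definition.** The Protocol article (Participants, under Exclusion criteria) describes the not-in-care cohort as adults with SMI who "do not receive specialized mental health care from a formal mental health care provider yet may receive social welfare/support". Support is optional in this definition, so people with no support at all belong to the cohort.

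**Size.** The same section starts from "the assumed average SMI prevalence of 1.6% among the adult population of the selected quarters (237,157 * 1,6% = 3795 people"), takes 24% of the SMI population as not in care, and adds: "Furthermore, around 90% of both groups lives independently (i.e. community dwelling"). It concludes: "On the basis of the aforementioned proportions, the not-in-care cohort is estimated to consist of 820 people". A 20% response rate is then applied.

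**Recruitment.** Participants and Recruitment not-in-care cohort name welfare and support organisations, among them organisations for homeless people, plus front-office and primary care services. At these services, "professionals from these services will be asked to select participants from their caseload based on client histories and their professional assessment". The services are listed with counts: 3 homeless shelter services, 1 financial and administrative support service, 2 social care services and 7 integral community support teams.

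**Claim.** The Abstract promises "A representative sample of community-dwelling adults with an SMI, including those in care" and those not in care. Study design and Discussion repeat the aim of representativeness.

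**Bias.** The Bias section accepts that both the choice of quarters and the recruitment method can cause selection bias. It then argues only that bias from the choice of quarters should be limited.

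**The concern.** The population that is defined and counted is wider than the population that can be recruited. An untreated adult who is on no caseload is counted in the 820 but has no stated chance of being interviewed. Being known to a service is a condition of entry, although the definition makes it optional.

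This matters because selection is tied to what the study measures. Research question 3 asks how formal and informal providers meet needs, and the CANSAS records whether each need is met and who provides the help. Recruiting everyone through a provider fixes part of that answer in advance. If the results are read as describing all untreated adults with SMI, those without any support are unobserved, and nothing in the results would show it.

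**Working it through.** **1. Reproduce the plan's figure.** Inputs: 237,157 inhabitants of the quarters (Setting); 1.6% prevalence, 24% not in care and 90% living independently (Participants).

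- 237,157 x 0.016 = 3,794.5 (stated: 3795)
- 3,794.5 x 0.24 x 0.90 = 819.6 (stated: 820)

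The figure reproduces. No term in it concerns contact with a service, so 820 is the estimated whole untreated, community-dwelling group.

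**2. Compare the two cohorts.** For the in-care cohort, Participants applies a provider-coverage factor (66%, taking 2884 to 1903). It also gives reasons for leaving out patients of other providers: the sample from the two large providers is expected to be representative, and recruiting at many small ones is unfeasible. For the not-in-care cohort there is no coverage factor and no reason for leaving out people known to no service.

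**3. What the planned yield implies.** At face value, 820 x 0.20 = 164, against a planned 150. If the 20% is a response rate among people reached through caseloads, then 150 / 0.20 = 750 people must be reachable, and 750 / 820 = 91.5%. The protocol also allows interviewed people to be excluded later on the SMI criteria, so 91.5% is a minimum if 150 is the final number.

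The true coverage is not given. Over an assumed range:

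| Assumed coverage | Reachable | Yield at 20% | Response needed for 150 |
|---|---|---|---|
| 100% | 820 | 164 | 18.3% |
| 75% | 615 | 123 | 24.4% |
| 50% | 410 | 82 | 36.6% |

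For comparison, the assumed in-care response is 33%.

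**4. Bias.** Suppose the recruits were a random sample of those on caseloads. The bias in a cohort mean or proportion would then be (1 - coverage) x (difference between people on and off caseloads). Neither term is in the document, so no value follows. The expression does show that recruiting more people from the same caseloads would not reduce the bias. Selection by professionals within the caseload comes on top of it.

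**The case against.** Several objections have force.

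- **The 20% may already absorb incomplete reach.** It is applied to the whole estimated cohort. On that reading the 91.5% falls away. The text calls it a response rate, however, and neither reading gives people without a service a way in.
- **The list of services may be open.** It begins "These include homeless shelter services (*n* = 3"), so 13 need not be the full number. This stands, but every source named, including those in Participants, is a service.
- **The risk is partly acknowledged.** The Bias section names the recruitment method, and Statistical methods speaks of proportions within the study population. The section offers no argument on recruitment, though, and the representativeness claim remains.
- **Caseload recruitment may be the only feasible route.** Accepted; the route need not change.

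Three stronger readings are tempting, and the document does not support them:

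- **That shelter clients fall outside the community-dwelling definition.** A reader might infer this from the reference to living independently. But Setting contrasts community-dwelling with residence in long-term clinical settings, and Exclusion criteria bars only home postal codes matching such locations. Recruitment through homeless organisations is openly stated. The share of participants who would come from shelters cannot be derived either, because service sizes are not given.
- **That met need will be overstated.** Service contact plausibly raises receipt of formal support. But professionals select clients for whom coordinated care is indicated, which could equally raise unmet need.
- **That an in-care versus not-in-care contrast is confounded.** No such contrast is named; Statistical methods refers only to unspecified comparisons between groups.

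**Conclusion.** The concern holds as a mismatch between the stated population and the recruitment frame. The protocol counts all untreated, community-dwelling adults with SMI in the quarters, recruits only through services that already know them, and calls the result representative without an argument for those left out. The design gives no basis for representing the full 24%; that is different from showing that a bias of a given size exists. Size and direction cannot be derived from the document. The required 91.5% coverage and the yields of 123 and 82 are illustrations: they rest on reading the 20% as a response rate among people reached, and the last two also on assumed coverage. This calls for a correction of stated scope and of reporting. The recruitment design can stand.

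**What to change.** 1. In the Abstract, Study design, Participants and Discussion, restate the cohort as adults with SMI not in specialised mental health care who are known to social support, shelter, front-office or primary care services. Limit the representativeness claim to that group. Present 820 as the estimated size of the whole untreated group, not as the recruitment frame.
2. Report prevalences and outcomes for this cohort separately from the in-care cohort. Do not present its receipt of formal support or its met needs as estimates for all untreated adults with SMI.
3. Optionally, describe results by housing situation, using the living-situation and housing items already listed under Sociodemographic variables.

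The cost is rewording and separate tables from data already planned, with no new participants. The price is a narrower stated target population.

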#### Recruitment LZA-cohort

Recruitment of former participants from the LZA-cohort will go in parallel to recruiting the in-care cohort at Arkin and GGZ inGeest, with the exception that the location criterion is not applied to this group. LZA-participants who are still in care at Arkin or GGZ inGeest will be added to the larger in-care cohort and no separate recruitment procedure is formulated. LZA-participants who are no longer in care at Arkin or GGZ inGeest will not be re-approached. LZA-participants who live in a clinical setting for a prolonged period of time will be approached by the fieldwork coordinator of the initial LZA-study. A more detailed description of the recruitment protocol of the LZA-study can be found in earlier publications [32, 45].

### Instruments and variables

#### Interview data

The current study focuses on the functioning of people with an SMI in important life-domains on the basis of five main themes: 1) sociodemographic characteristics, 2) social functioning, 3) safety and discrimination, 4) substance use and life events, 5) subjective appraisal and recovery and 6) health. Each of these themes is addressed by distinct outcomes, that will be assessed with validated instruments. The selection of instruments included matches the instrumentation of the LZA-study to a large extent, thereby enabling a third wave of the LZA study. Table 1 present an overview of all instruments included in the study protocol.

**Table 1 Tab1:** Overview of the instruments included in the questionnaire

Domains and outcome measures	Instrument	No. items
Social functioning		
Social network	Social network questionnaire (SNQ)	14
Social support	Inventory for social support (ISS)	11
Loneliness	Loneliness scale (De Jong-Gierveld)	6
Social participation	Items from health of the nations outcome scale (HoNOS)	4
Social exclusion	Social exclusion index (SEI)	19
Safety and discrimination		
Subjective safety and victimization	Integral safety monitor (ISM)	27
Discrimination	Daily discrimination scale (DDS)	9
(self)stigmatisation	Stigma scale (S-scale)	28
Substance use and life events		
Substance use and dependency	Measurement for triage and evaluation (MATE)	9
Alcohol use disorder	Alcohol use disorder identification test (AUDIT)	10
Substance use disorder	Drug use disorder identification test (DUDIT)	10
Negative life-events	List of threatening experiences (Brugha)	12
Subjective appraisal and recovery		
Quality of life	Manchester short assessment of quality of life (MANSA)	16
Recovery	Integral recovery scale (symptomatic, social, personal) (IRS)	13
	National recovery scale (personal recovery)	26
Health		
Physical health	RAND SF-36 Health Survey	12
Needs for care/support	Camberwell assessment of need short appraisal schedule (CANSAS)	25
Psychopathology severity	Brief psychiatric rating scale (BPRS)	24

##### Sociodemographic variables

Sociodemographic variables included are age, gender, cultural-ethnic background, education status, living situation (e.g., alone, with a spouse and/or children, in a group, with parents), type of housing, work/education/daytime activities (i.e. societal participation) and family situation.^1^

##### Social functioning: social network

The Social Network Questionnaire (SNQ) [47] will be used to determine the size and composition of one’s social network. The 14-item instrument covers several categories of social contacts (e.g., family, work, education) and counts the total number of social contacts reported and the number of concrete social contacts in the preceding month. The instrument distinguishes between one’s primary and secondary social network. The SNQ has been tested for validity and reliability (alpha = .82) [48] in determining network size and frequency of contacts.

##### Social functioning: social support

The Inventory for Social Support (ISS) is a self-report instrument that measures social support [49]. More specifically, the 12-item instrument measures subjectively experienced support received from one’s most important social contact. The ISS distinguishes between emotional and practical support. Psychometric properties of the ISS are satisfactory, as demonstrated by its internal consistency and convergent and divergent validity [50].

##### Social functioning: loneliness

Feelings of loneliness will be measured with the short version of the loneliness-scale [51, 52]. The instrument measures the extent to which one’s social contacts satisfy one’s need for social contact/interactions. Participants indicate the extent to which they agree with 6 statements (e.g., *I miss having people around me*, *There are plenty of people I can rely on when I have problems*) with a score ranging from 1 = *No!* to 3 = *sort or less* to 5 = *Yes!*. The instrument includes a total loneliness score and two subscales: social loneliness and emotional loneliness. The loneliness scale and its’ subscales have been shown to be reliable and valid in several countries [51] and among several ethnic target populations [53].

##### Social functioning: social exclusion

The Social Exclusion Index for Health Surveys (SEI-HS) is a 19-item instrument [54–56] designed to measure social exclusion according to the following subdomains: social participation (e.g., *I feel isolated from other people*), material deprivation (e.g., *Does your household have enough money to visit family or friends?*), access to basic social rights (e.g., *How satisfied or dissatisfied are you with the quality of your home?*), normative social integration (e.g., *I occasionally do something for my neighbors*) and perceived social exclusion (e.g., *the feeling of being isolated from society*). A person is socially excluded in case of accumulation of disadvantages in four subdomains. The SEI-HS has been demonstrated to have adequate internal consistency for the general index and satisfactory construct validity [57].

##### Safety & discrimination: subjective safety and victimization

Victimization will be measured with the Integral Safety Monitor (ISM) [58]. The instrument is used in the context of a yearly national monitor study of the Dutch Ministry of Safety and Justice, performed by Dutch municipalities. The ISM is a self-report instrument that includes the assessment of neighborhood livability, subjective safety and victimization of 15 different types of crimes among which violent crimes (e.g., battery/assault, sexual violence), nonviolent crimes (e.g., theft, home burglary) and cybercrimes (e.g., identity theft, cyber bullying). The IVM has, to our knowledge, not been tested for its psychometric properties. However, it is considered an adequate and well-structured instrument to gather self-reported information about victimization [58]. Self-report is considered to be more reliable and accurate than using information from objective registries that tend to underreport victimization (e.g., police, public prosecutor) [59].

##### Safety & discrimination: discrimination

The Dutch translation of the scale for daily discrimination of the National Survey of “Midlife Development in the United States” [60, 61] will be used to assess personal experiences with discrimination. The scale includes 7 types of discrimination, that are assessed with 9 Likert-type items (e.g., *How often do you experience being treated less politely than other people)* with answer categories ranging from 1 = *often* to 4 = *never*. Levels of daily discrimination are measured according to a total score of the recoded 9 items with higher scores indicating higher perceived discrimination. The internal consistency of the discrimination scale is high (alpha = .97) [61].

